#### Physical activity, sedentary time, and sleep time

An ActiGraph GT3X + accelerometer (ActiGraph, Illinois, United States) will be utilized for device-based measurement to monitor physical activity, sedentary behavior, and sleep time. The accelerometer has been validated for assessing physical activity, sedentary behavior, and sleep quality (48, 49).

Participants will be instructed to continuously wear the device on their non-dominant wrist for 7 days (24 h/day) and only remove it for water activities. Wrist-worn accelerometers have become popular because they place a low burden on participants and provide valid and reliable measurements of physical activity (50). Accelerometers will be initialized to a sampling rate of 100 Hz and downloaded using ActiLife^®^ software (ActiGraph, Pensacola, FL). The raw accelerometer data (.gt3x) will be processed using the GGIR 3.0–5 package (51), in R studio. The minimum amount of accelerometer data that will be considered acceptable will be 600 min of valid daily monitor wear on at least 4 days including a weekend day (52, 53). The MVPA threshold and cutoff points used will be those proposed by Hildebrand et al. (54, 55). Sleep time (periods without z-angle changes of >5° for at least 5 min) will be calculated using an algorithm proposed by van Hees et al. (56), and identification of onset and wake time will be guided by the HDCZA algorithm (51). All participants start with their pre-intervention and post-intervention measurements on the same dates, in order to maintain the same measurement conditions for all and reduce the risk of bias.

To complement the accelerometer data, we will administer four questionnaires: (a) the Physical Activity Questionnaire (GPAQ), a standardized tool recognized by the World Health Organization that provides valuable information on physical activity levels globally (57), (b) a single physical activity question to identify the level of physical activity through a single item (58), (c) the Occupational Sitting and Physical Activity Questionnaire (OSPAQ) will be used to determine the proportion of time participants spend on sedentary behavior during work hours (59), and finally, (d) the Daily Activities Behavior Questionnaire (DABQ) to gather additional information on participants’ physical activity, sedentary behavior, and sleep habits over 24-h (60). Questionnaire will also be used to categorize participants as non-participants in physical exercise programs according to our exclusion criteria. Questionnaires b, c, and d will be validated in Spanish in a parallel study by our investigation group. The combination of device-based measurement tools and standardized questionnaires will enable an accurate and comprehensive assessment of physical activity levels, sedentary behavior, and sleep quality. All of these variables will allow us to analyze the effect of reducing sedentary time and its impact on the study’s objective (61, 62). The data collected will be crucial for analyzing the results and effectiveness of interventions among office workers.

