#### Sample size calculation

The sample size was calculated using the G*Power software. This calculation considered the repeated measures of factorial analysis of variance (ANOVA), with an effect size (f) of 0.20, alpha value of 0.05, and beta of 0.80. The study involved three groups and two evaluation time points (pre/post), with an estimated follow-up loss of 10%. Consequently, 60 participants will be distributed as 20 participants per group: two experimental groups (B-B led by professionals and unled C-P) and one control group. The groups will be sex balanced because of the predominance of women in this type of work. In this sense, for selecting participants, we used the sex ratio of workers in group B-B (the lowest men proportion). In this site, there is a proportion of 27.1% of men and 72.9% of women; thus, our sample will try to approach this proportion in the two remaining groups.

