#### Procedures

The project will be conducted in three stages, comprising two visits to the Physical Performance and Health Laboratory of the PUCV (stage one and stage three) and one visit to the participants’ offices (stage two). Previous to measurement sessions, participants will be asked not to consume any type of stimulant prior to the measurements (such as caffeine or tea, mainly for blood pressure and heart rate). The first stage will consist of a pre-intervention measurement session in our laboratory, in which cardiometabolic risk factors, stress perception, occupational pain, physical activity, sedentary time at work, 24-h behavior, eating and smoking habits, and sociodemographic information will be evaluated. In addition, participants will be given an accelerometer, which will be removed 7 days later, and the intervention will begin once the accelerometer is removed. The intervention will have a total duration of 12 weeks, because previous literature indicates that 12 weeks is sufficient time to observe behavioral changes that can be extended beyond the time of the intervention (44). In the second stage (sixth week of intervention), the three groups will receive accelerometers to re-evaluate their daily physical activity intensity, sedentary time, and breaks in sedentary time. Finally, the third stage (post-intervention measurement) will consist of a second visit to our laboratory, where all variables will be re-evaluated. The anonymized and raw data obtained will be made available by the corresponding author upon reasonable request. A diagram of the study design, sample, and measures is presented in Figure 1.

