### Main variables

In the first stage, upon arrival at the laboratory, participants will be asked to read and sign an informed consent form and then begin the measurements. First, the participant will be asked to complete questionnaires (stress perception, occupational pain, physical activity, sedentary time at work, 24-h behavior, eating habits, smoking habits, and socioeconomic status). Subsequently, the participants will be asked to enter the DXA room in the laboratory, where their height, weight, and waist circumference will be assessed. Once these measurements have been taken, the participant will be asked to lie on the scanner table for analysis. Upon completion of the scanner (estimated duration of 7 min), the participant’s resting heart rate will be determined while they remain in a lying down position. Thereafter, the individual will be requested to sit down, and their blood pressure will be measured in their left arm twice consecutively. After this, handgrip strength will be measured 2 times for each hand. Lastly, the accelerometer will be provided to the participant for a period of 7 days, for the initial measurement.

In the second stage, our research team members will go to the participants’ workplaces for the second delivery of accelerometers for 7 days. In the third stage, participants will be administered questionnaires (stress perception, occupational pain, physical activity, and sedentary time at work). Subsequently, measurements of cardiometabolic risk factors will be made with the previously mentioned protocol. All measurements will be carried out between 16:00 and 20:00 for the convenience of the participants due to their work schedule. Is important to note that all the factors chosen in this work are relevant for public health research since they are social determinants of importance for the design of public policies in our specific population.

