However, this trial has limitations. First, randomization will not be possible due to the intervention’s characteristics as well as blinded allocation. Second, for the participants’ convenience, compositional measurements were scheduled in the afternoon. This may impact the measurements due to the participants’ hydration and food intake status. Nevertheless, in order to minimize the risk of measurement errors, particularly those related to the time of day, the same measurement protocol will be followed for all participants (83). Third, stress perceived by desk-based workers will be measured through a questionnaire, and exercise intensity will be gaged by RPE. In both instances, it would be desirable to incorporate complementary physiological indicators, such as cortisol levels and heart rate, respectively. Fourth, although the accelerometer allows to determine the sitting and break time, it is not completely appropriate to determine the stationary postures as other devices (e.g., inclinometers) (52). Additionally, our assessment of cardiometabolic risk factors does not encompass a lipid profile.

This study also has strengths to highlight. First, although the OSPAQ, DABQ, and single item of the physical activity questionnaire are not validated in Spanish language, our research group is actively working on these validations in a parallel study. Second, the intervention during 12 weeks already allows to observe behavioral change (44), which could extend in time the effects of the interventions carried out after the study’s end. Thirdly, integrating both device-based and traditional measures for cardiometabolic risk, physical activity, and sedentary lifestyle will enable the creation of a more comprehensive model to understand the effect of two protocols of active breaks at work in our outcomes. In this regard, it is important to remark on the use of DXA for body composition measurements, in contrast to the measures most commonly used in previous studies (i.e., BMI, waist circumference). Fourth, the determination of specific covariates that may affect our outcomes in important ways. These covariates will allow us to adjust our analysis model in order to comprehensively explore the effects of the intervention proposed in this study.

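### The same-dates safeguard can only mean a measurement period of at least two days (if there is one scanner), and the four-hour window leaves each person's pre and post clock times unmatched

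*Protocol article*

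**What the plan says.** The accelerometer section (Physical activity, sedentary time, and sleep time) closes with a safeguard: "All participants start with their pre-intervention and post-intervention measurements on the same dates, in order to maintain the same measurement conditions for all". The rest of that sentence gives reducing the risk of bias as a further purpose.

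Main variables sets the daily window: "All measurements will be carried out between 16:00 and 20:00 for the convenience of the participants due to their work schedule". The same section gives the order of the laboratory visit:
- consent and questionnaires;
- height, weight and waist in the DXA room;
- the scan;
- resting heart rate while still lying down: "Upon completion of the scanner (estimated duration of 7 min), the participant’s resting heart rate will be determined";
- blood pressure, then handgrip;
- the accelerometer, handed over last.

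Procedures links the start of treatment to that device: "the intervention will begin once the accelerometer is removed". It also asks participants to avoid stimulants before measurement, mainly for blood pressure and heart rate.

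In the Discussion (Expected results and transfer to the work context), the limitations paragraph accepts that afternoon scheduling may affect the measurements through hydration and food intake. Its answer is that "in order to minimize the risk of measurement errors, particularly those related to the time of day, the same measurement protocol will be followed".

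**The concern.** The article offers two protections for comparability: shared dates, and a common protocol against time-of-day error. Neither is fixed tightly enough to do the work claimed for it.

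On dates, the device is issued at the end of a visit that includes a scan. A literal common start date would therefore need everyone through the scanner on the same day. If that cannot be done, the sentence must describe a period, and the article does not say how long the period is or whether the arms are mixed within it.

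On clock time, the outcomes are changes within a person from pre to post. A protocol that is the same for all participants does not make one person's two visits alike. If someone is scanned early in the window at baseline and late at follow-up, food and fluid taken in between become part of the measured change. The intervention is brief light-to-moderate activity over 12 weeks, so avoidable noise in DXA mass, blood pressure and heart rate makes any effect harder to detect.

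**Working it through.** The article gives no figure for throughput or number of visit days, so there is no stated result to reproduce. The check is capacity arithmetic.

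**Inputs**
- Participants: "60 participants will be distributed as 20 participants per group" (Sample size calculation). The same section allows 10% loss to follow-up, so 60 × 0.9 = 54 at the post visit.
- Scan time: 7 min (Main variables).
- Daily window: 16:00 to 20:00 = 240 min (Main variables).
- Scanners: one. This is an assumption. Main variables describes one DXA room and Cardiometabolic risk factors gives one series number, but the count is not stated.

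**Can one round fit in one day?**
- Scan time needed at pre: 60 × 7 = 420 min, more than 240 min.
- Scan time needed at post with 54 people: 54 × 7 = 378 min, still more than 240 min.
- Most people per day on scan time alone: 240 / 7, rounded down = 34.
- Days needed: 60 / 34, rounded up = 2.
- To finish 60 people in one day, each could have only 240 / 60 = 4 min.

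Seven minutes is a floor, because height, weight, waist and resting heart rate are also taken in the room or on the table. The time for these is not stated, so a range is assumed:

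| Room time per person (assumed) | People per day | Days for 60 |
|---|---|---|
| 10 min | 24 | 3 |
| 15 min | 16 | 4 |
| 20 min | 12 | 5 |
| 30 min | 8 | 8 |

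**How far apart can one person's two scans start?**
- The earliest start is 16:00. The latest start that still finishes by 20:00 is 20:00 less 7 min = 19:53.
- Largest difference: 240 − 7 = 233 min, and 233 / 60 ≈ 3.9 h.

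This is an upper limit. If the whole visit must fall inside the window, the limit is 240 min less the visit length. An assumed 60-min visit, for example, gives 240 − 60 = 180 min.

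**What limits that difference?** Setting the sections side by side, the only stated controls are the four-hour window and the request about stimulants. The article states no food or fluid instruction and no matching of a person's post visit to the baseline clock time.

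**The case against.** A reader might infer that the plan promises something impossible. The documents do not support that. It would need the safeguard to mean a single calendar day and the laboratory to have only one scanner. The word for dates is plural, the verb concerns starting, and the sentence sits in the accelerometer section. It reads naturally as a common period for all three groups, and a period of a few days is feasible. The number of scanners is not given, and two running in parallel would clear 60 people in one day on scan time alone. This objection stands, and the point is therefore about clarifying the statement, not about a contradiction.

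A reader might also infer that calendar date is confounded with arm, because arms are formed by work site and controls come from another institution. No section says that visits will be booked site by site. On the shared-period reading, the safeguard is a commitment to measure the arms at the same time. Confounding is a risk if booking follows site, and not something the plan sets up.

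On time of day, the authors disclose the limitation, speak of minimising error and not of removing it, and do restrict visits to one part of the day. A gap of hours within a person is permitted, not planned, and nothing suggests it would differ by arm. Finally, appointment rules often sit in a full protocol or manual that an article condenses, so their absence alone would be no finding. What remains is that the article itself names the common protocol as the protection against time-of-day error, and the rule it states does not act on the within-person comparison.

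**Conclusion.** The point holds as an inexpensive improvement to a stated safeguard, not as an error in the plan. With one scanner (assumed), the same-dates sentence can only describe a period of at least 2 days per round, or 3 to 8 days if room time is 10 to 30 min per person (assumed). The stated window lets one person's pre and post scans start up to 233 min, about 3.9 h, apart. The expected consequence is extra noise in within-person change in DXA mass, blood pressure and heart rate. How much noise cannot be computed, because the article gives no figures for variation over the afternoon or for intake between visits.

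**What to change.** Make two changes of wording and scheduling.

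1. Replace the same-dates sentence with a common date window at pre and another at post. State the length of each, and say that all three arms are spread across its days.
2. Book each person's post visit within about 60 min of that person's baseline clock time, and give the same food and fluid instruction before both visits.

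No visit, procedure or outcome is added. Participants lose a little flexibility in booking. There is also a planning cost: booster breaks run in groups of 4–5 and the intervention starts when the accelerometer comes off. Members of one group should therefore have baseline visits close enough together to keep their start dates aligned while the arms remain mixed across the window.

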#### Stress perception

The Perceived Stress Scale Questionnaire (PSS-14) will measure stress perception in various situations. This questionnaire was initially validated by Cohen, Kamarck, and Mermelstein in 1983 (63) and has been adapted for use in Chile by Erik Marín (64). The PSS-14 questionnaire assesses an individual’s perception of different situations in which their stress levels may be influenced. The questions focused on the last month and are rated on a Likert scale ranging from 0 to 4 (0 = never, 1 = rarely, 2 = sometimes, 3 = often, 4 = very often). To obtain the total PSS score, the scores of items 4, 5, 6, 7, 9, 10, and 13 are reversed (0 = 4, 1 = 3, 2 = 2, 3 = 1, 4 = 0), and then the 14 items are summed. A higher score indicates a higher level of perceived stress.

#### Occupational pain

The Nordic Musculoskeletal Questionnaire, a standardized tool recommended by the Institute of Public Health of the Chilean Ministry of Health, will measure occupational pain. This questionnaire is specifically designed to detect musculoskeletal symptoms related to desk-based work, including pain in the neck, shoulder, thoracic spine, wrist, lumbar spine, hip, knee, and ankle (65). This questionnaire uses closed-ended (yes or no) questions regarding the prevalence of pain in the aforementioned joints, which facilitates obtaining dichotomous pain categories per joint, per participant. With the implementation of this tool, we will be able to assess both the general and specific pain experienced by participants in the workplace. This method provides a comprehensive evaluation of the prevalence and severity of musculoskeletal pain, enabling a thorough analysis of the overall impact on employees’ well-being (18, 66, 67).

#### Other measurements (covariates)

Previous studies have established that cardiometabolic risk factors are not only affected by body composition, physical activity, or sedentary behavior but can also be influenced by various healthy lifestyle habits (30–32). Therefore, we identified a series of related factors that will be included as covariates in our statistical analyses to assess their impact on our outcomes.

We will use an ActiGraph accelerometer to measure sleep quality (48, 49). This variable plays a fundamental role in cardiovascular health (68). Lack of quality sleep can increase blood pressure and inflammation by increasing cortisol levels and decreasing immunity, elevating the risk factors for cardiovascular problems (68).

The questionnaire on adherence to the Mediterranean diet will be applied to assess eating habits, specifically designed to measure participants’ adherence to it and determine its relationship with cardiometabolic factors (69–71). This questionnaire gathers information on the frequency of consumption of foods characteristic of the Mediterranean diet using a Likert scale format. To assess participant adherence, the score of each question is summed to obtain a total score, reflecting the individual’s adherence to the Mediterranean diet.

The Fargerstörm test, which scores various aspects of smoking habits on a Likert scale and enables us to determine the level of dependence on this substance, will be used to assess smoking habits (72).

Furthermore, we will obtain information on the participants’ socioeconomic status using a questionnaire on the distribution and average autonomous income of households by income deciles. This questionnaire provides essential data on the *per capita* income of the participants and follows the guidelines of the “Asesoría Técnica Parlamentaria” of the Chilean government (73). In addition, the educational level and occupational status of the participants will also be recorded. These measures are considered relevant as predictive cardiometabolic risk factors (70, 74, 75). In addition, sociodemographic questions will be asked to characterize the study sample.

### Protocol interventions

#### Computer prompts group (unled breaks)

Active breaks during the workday will be guided by an application called “Ponte de Pie por tu Salud” developed by the Chilean Ministry of Health.^1^ The exercises included in these breaks focus on stretching, mobility, and muscular resistance with light to moderate intensity (i.e., Rate of Perceived Exertion [RPE] 3–4) following the Chilean Safety Association (*Asociación Chilena de Seguridad*—ACHS) recommendations (76, 77). An example of the exercises to be performed can be found in the following link (See Footnote 1). The sessions will begin with a warm-up and end with a cool-down, following the ACHS guidelines. The application is configured to generate 2-min breaks every hour for 8 h per day, ensuring that participants accumulate an average of 14–16 min of active breaks each day.

#### Booster breaks group (led breaks)

We will implement active breaks lasting approximately 14 to 16 min every working day for 12 consecutive weeks, for five workdays, excluding weekends. By implementing this approach, we can ensure that both interventions are distributed equally over time. These breaks will consist of breathing exercises, stretching exercises, and exercises recommended by the ACHS (76, 77). They will be similar in intensity to exercises proposed in the “Ponte de Pie por tu Salud” application. Each session will be divided into three parts: warm-up (2 min), main work (12 min), and cool down (1 min). The intensity of the exercises will range from light to moderate (RPE 3–4), and at the end of each session, we will evaluate intensity perception using Borg’s scale (78). Trained personnel from our research team will conduct all the sessions throughout the intervention. The intervention will be conducted in small groups (4–5 participants). While this may have a different impact on stress or motivation than the computer prompts group breaks, this is a limitation inherent to the type of intervention (22).

During the warm-up period, we will include breathing and muscle activation exercises that will last approximately 2 min. For the main work, we will target four main muscle groups: neck and shoulders, arms and wrists, lumbar back and hips, and knees and ankles, which will be distributed and combined according to Table 1.

**Table 1 tab1:** Graphical example of the time distribution of muscle groups in 1 month of intervention.

Days	Week 1	Week 2	Week 3	Week 4
Monday	i 70% - ii 30%	ii 70% - i 30%	i 70% - ii 30%	ii 70% - i 30%
Tuesday	iii 70% - iv 30%	iv 70% - iii 30%	iii 70% - iv 30%	iv 70% - iii 30%
Wednesday	i 70% - iii 30%	iii 70% - i 30%	i 70% - iii 30%	iii 70% - i 30%
Thursday	ii 30% - iv 70%	iv 30% - ii 70%	ii 30% - iv 70%	iv 30% - ii 70%
Friday	iv 30% - i 70%	i 30% - iv 70%	iv 30% - i 70%	i 30% - iv 70%

B-B, Booster Breaks group; (i) neck and shoulders, (ii) arms and wrists, (iii) lumbar back and hips, and (iv) knees and ankles. The program will be cycled over the next 2 months. Please refer to the Supplementary material for more information on the session and exercises to be implemented.

To prevent participant dropout and maintain motivation throughout the intervention, both variations and combinations of the main muscle groups to be worked on will be introduced. The two muscle groups will be combined daily, with 70% of the time allocated to the first group and 30% to the second group. The order and time percentages will be reversed the following week. In the second month, elastic bands and canes will be incorporated to support the exercise performance. The main work session will last nearly 12 min.

It is important to note that although B-B includes exercises that differ from those of the application, the intensity will be the same. Borg’s scale will be employed for this purpose to ensure comparability between the interventions. In this sense, our investigation group conducted a pilot test of the selected exercises to determine the correct intensity in relation to the exercises proposed by the application. In addition, the staff in charge of conducting the group B-B active breaks ensured that the sessions were performed between light and moderate intensity (i.e., RPE 3–4). Participants played an indirect role in the validation of the intervention’s B-B component. Although no focus group was conducted to directly gather their input for the intervention’s design, which is based on government programs, their well-being at work was taken into account when creating the exercise plans (for instance, the subjects did not wish to perspire, so the exercises were of mild to moderate intensity). Furthermore, it should be emphasized that the participants in both intervention groups are affiliated with the institution where the principal investigators are employed, thus providing a known context for the participants.

